### Data collection

The data collection will be at three time points the first will be at baseline (T0), the second will be immediately after the 12-week intervention (T1) while the third will be three months after the intervention (T2). Details in Table 1. The data collection will employ a mixed methods approach including:(i)A desk review of relevant state and national NCDs prevention policies and guidelines on physical activity and an assessment of the level of coherence of the School Health Promotion policy with these policies. Other documents which will be reviewed include the Physical Health Education curriculum and school timetable to assess the opportunities for PA during school hours. The policies which regulate the construction of schools will also be reviewed to assess the extent to which these documents regulates or influences the built environment and physical activity levels in school.(ii)Physical and Health Education Teachers will complete the School Physical Activity Policy Assessment tool (S-PAPA) – a standardised semi-structured tool which assesses physical education, recess and other physical activity opportunities before, during and after school [31]. For this study, only two components will be assessed - physical education and recess. Scores on the S-PAPA tool will be tabulated based on policies and practices identified as being related to children’s physical activity during school [32, 33]. Total point scores will also be either median-split into high- and low or stratified by percentile for analysis [34].(iii) Focus Group Discussions and In-depth interviews will be held with teachers and school principals respectively to assess their opinion about social norms and support and the extent of implementation of physical activity policies and programmes in schools, level of funding, and the frequency of engagement in structured physical activity. Observations will be conducted to document facilities for physical activity in the schools using the Sport, Physical Activity and Eating behaviour: Environmental Determinants in Young people (SPEEDY) checklist. The SPEEDY checklist measures the built environment of schools and can be scored to quantify environmental support for physical activity [35]. The checklist assesses school-level environmental variables such as *Walking Provision, Cycling Provision, Aesthetics, Sport and facility provision, Other facility and Design of the school grounds* [36] The scores from each of the key variables will be dichotomised into low and high based on percentiles, and the school physical activity suitability index will be computed [36, 37].(iv) A cross sectional survey will be conducted among the students using an adapted version of the *Physical Activity Questionnaire for Adolescents (PAQ-A)* [38] to generate self-reported data on the level of physical activity among young people. The PAQ-A is a self-administered, 7-day recall instrument. It was developed to assess general levels of physical activity for high school students approximately 13 to 19 years of age. It assesses the frequency of participation in physical activity during spare time, physical education period, lunchtime, after school, in the evenings and on weekends. A summary of the physical activity score is generated from the mean of 8 items, and ranges from 1 to 5, with higher scores indicating more frequent participation in physical activity [38]). The physical activity levels will be categorised into three; low physical activity level will be those who score between 1 to 1.9 while moderate and high physical activity levels will be those who score between 2 to 3.9 and 4 to 5 respectively [13]. For some statistical analyses, the self-reported physical activity level will be treated as a continuous variable. In a study to establish the convergent validity of the PAQ-A, the instrument was found to be significantly correlated to all self-report measures (including activity rating, *r* = 0.73; Leisure Time Exercise Questionnaire, *r* = 0.57; and 7-day physical activity recall interview, *r* = 0.59) [39]. The survey will also assess the frequency of engagement in structured physical activity from two time points (baseline and follow up) as the primary outcome measure. Based on the theory of Planned Behaviours which is the theoretical framework guiding this intervention, other variables which will be incorporated into the Physical Activity Questionnaire for Adolescents (PAQ-A) are the measures for attitude, subjective norms, perceived behavioural control and self-efficacy. A research tool which was theoretically derived by Motl et al., 2000 based on Theory of Reasoned Action (TRA) and Planned Behaviour (TPB) and Social-Cognitive Theory (SCT) will be used to assess the social-cognitive factors among this young people. This questionnaire has been tested and evidence provided for its factorial validity as a unidimensional measure of attitudes, subjective norms, perceived behavioural control and self-efficacy about physical activity among adolescent girls [40]. The core variables i.e. *knowledge of health benefits of physical activity, attitude, subjective norms, perceived behavioural control and self-efficacy about physical activity* will be analysed by scoring and summing up all question items and cut-offs will be determined using percentiles.The survey will be complemented with focus group discussions to assess their opinions about the individual, social, community, institutional and policy factors which influences the physical activity behaviours of young people.(v)Anthropometric and other physical measurements (body-mass-index for age, waist-to-hip ratio, blood pressure) will be documented. Anthropometric measurements will be taken twice and averaged; for discrepancy >10%, a third measurement will be taken. The height and weight will be assessed using standard anthropometric procedures. Height will be measured using a portable height meter/stadiometer. Students will be asked to take off their shoes and stand with their back to the portable height meter/stadiometer. The sliding bar will be lowered and pressed flat on the head and recorded to the nearest centimeter. Body weight will be measured using a digital scale and weight will be recorded to the nearest gram. Age -and sex -specific prevalence of overweight and obesity will be determined by the body-mass- index for age Z scores using the criteria defined by the World Health Organisation (WHO). According to the WHO cut off points; overweight is considered to be > + 1SD (equivalent to BMI 25 kg/m2 at 19 years), Obesity: > + 2SD (equivalent to BMI 30 kg/m2 at 19 years), Thinness: <-2SD, Severe thinness: < −3SD and Normal: > −1 to < +1 SD. Standard deviations (Z-scores) will be computed using the World Health Organisation (WHO) reference population, 2007 soft ware (Anthropometric Software Program, Version 1.0.4 [41]. Blood pressure will be measured and the mean of three measurements will be recorded. Referrals will be initiated for children whose blood pressure exceeds the 95th percentile for age. Waist circumference will be measured to the nearest 0.1 cm horizontally at the narrowest point between the lower end of the rib cage and iliac crest. Hip circumference will be measured to the nearest 0.1 cm, at the greatest horizontal circumference below the iliac crest at the level of greater trochanter. Waist hip ratio will be obtained as waist circumference/hip circumference.The fitness level of the adolescents will be measured using the 20-m shuttle run test (20-mSRT) also known as the multi-stage fitness test. The 20-mSRT is the most widely used field-based test for aerobic fitness in young people and UK percentile data and health-related cut points are available [42]. A systematic review recently concluded that the 20-mSRT is the most reliable and valid field based method to estimate aerobic fitness in young people [43]. Performance in the 20-mSRT is typically expressed as laps, levels or distance completed. The 20mSRT estimates the cardiorespiratory fitness (aerobic capacity). Children run back and forth between two lines 20-m apart following beep signals played from a pre-recorded CD. The pace of the test is ramped such that running speed increases by 0.5 km/h each minute or period. The test is finished when the child stops owing to fatigue or when he/she does not reach the line in time with the audio signal on two consecutive occasions [44]. The last completed run indicates the final result of the test. The physical fitness data will be analysed and used as continuous variables and an increase in test results will indicate higher physical fitness [45].(vi) Step count will be recorded using a pedometer. During the data collection process, 100 students (10% of the sample) will be asked to wear a Yamax SW200 Step Digi-Walker pedometer on their right hand for seven consecutive days, except during sleep and water based activities. Text messages/phone calls will be made daily as reminders to ensure compliance. The pedometers will be sealed with a sticker or cable to prevent reactivity i.e. a situation where individual change their normal activity pattern as a result of being monitored.The pedometers will be worn daily for seven days with a minimum of 4 valid days. Step counts of less than 1000 steps per day and greater than 30,000 steps per day will be treated as missing data [46]. Step count of 10,000 to 11,700 and over will be recorded as achieving the daily recommended levels of 60 min of MVPA in adolescents [47].

**Table 1 Tab1:** Data Elements to be collected, Study Timepoints (T0, T1, T_2_), Target Groups

Objectives		Measure	Study instruments/Methods	Target group	Schedule		
					T_0_	T_1_	T_2_
Assess the pattern of physical activity among in-school adolescents		• PA Behaviours • Fitness	• PAQ-Questionnaire • Pedometers • 20-mSRT	Students	x	x	X
Identify factors (individual, social-cultural, built environment and policy) influencing physical activity of in-school adolescents	Individual	• Knowledge on PA, attitude, subjective norms (*normative beliefs and motivation to comply*) perceived behavioural control (*control beliefs and influence of control beliefs*), behavioural intentions and other demographic variables • Weight, Height, Waist-Hip circumference • 20-mSRT	• Questionnaire Focus group discussion guide • Anthropometric measurements • 20-mSRT	Students	x	x	x
	Socio -cultural environment	Social Norms Social support	• Key Informant Interview guide • Semi structured • Questionnaire • Focus Group Discussion guide	(i)Principals (ii)Officials of Ministries of Education, Health, Sports Physical and Health Education Teacher Classroom Teachers	x	x	x
	School’s built Environment	school grounds and safety, physical activity and recreation facilities aesthetics	• Observation using the SPEEDY Checklist	School Environment	x		x
	Policy	• PA Policies/programme • Extent of integration of recommendations in global and national policies and guidelines on physical activity for NCD prevention into the Nigerian school health policy	• Key Informant Interviews • Data extraction tool for Desk Review and Policy Analysis	(i) Principals (ii) PHE Teachers (iii) Officials of Ministries of Education, Health, Sports	x		x
Assess the effect of a multi-level intervention on the physical activity levels of secondary school students		• Knowledge on PA, attitude, subjective norms (*normative beliefs and motivation to comply*) perceived behavioural control (*control beliefs and influence of control beliefs*), behavioural intentions and other demographic variables • Weight, Height, Hip and Waist circumference • Fitness level	• Questionnaires • Pedometers • Anthropometric measurements • 20-mSRT	Students	x	x	x

T0: Baseline measurement

T1: Measurement immediately after the intervention

T2: Measurement three months after the intervention

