## Abstract

**Background:**

Physical inactivity contributes to the global burden of non-communicable diseases. The pattern of physical activity in adulthood are often established during adolescence and sedentary behaviours in the early years could influence the development of diseases later in life. Studies on physical activity in Nigeria have focused largely on individual behaviours and the effects of school-based interventions have not been well investigated. The aim of the proposed study is to identify factors influencing; and evaluate the effects of a multi-level intervention on the physical activity behaviours of in-school adolescents in Oyo state, Nigeria.

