### Blinding and sampling technique

Multistage sampling technique will be used for the study. Nigeria is divided into six regions with approximately six states each. The south west region was purposively selected for this study.Step 1:The study state was selected randomly from the six states in the south west region of Nigeria.Step 2:Two comparable Local Government Areas (LGAs) in the project state will be selected using simple balloting. The list of LGAs was stratified based on their socio-economic status and level of urbanisation. One of the LGAs will be the experimental while the other will serve as the control.Step 3:The list of schools will be obtained for the selected LGAs and stratified by ownership i.e. public and private and population size. Twenty two schools will be pair-matched based on their ownership (i.e. public and private) and population size and randomly allocated to either the experimental (11 schools) or control (11 schools) group by simple randomisation by an independent researcher not involved in the study.Step 4:The male and female student ratio for the selected schools will be obtained and used for the determination of students to be selected for each school disaggregated by sex. The selected in-school adolescents will serve as the index children though all the students in the schools allocated to the experimental group will be exposed to the intervention.Step 5:The number of arms for classes from each school will be documented and two arms of classes at each level in the school will be selected by balloting for the study.Step 6:Study participants in each class will be selected using systematic random sampling technique based on the male to female student ratio and expected cluster size for the school.Step 7:The selected respondents will be enrolled as a cohort in the experimental and control schools and followed up after the 12-week intervention.

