#### Data management and statistical analysis

Serial numbers will be assigned to the questionnaires for easy identification and recall of the instrument and these will be stored in a place safe. A coding guide will be developed and sections of the tools which are open ended will be coded before data entry. The data will be cleaned to identify and correct all errors. The quantitative data will be analyzed using STATA version 13.

There are two key primary outcome variables specifically step count measured with pedometers which is a continuous outcome variable and self-reported physical activity level which can be a continuos or ordered categorical variable, details in Table 4.

**Table 4 Tab4:** Description of outcome Measures

	Description of outcome measures	Type of Variable
Primary Outcome Measures	Self-reported physical activity score/levels	Continuous
		Ordered categorical
	Step count (average steps/day)	Continuous
Secondary Outcome Measures	Anthropometric Measurements (measured using body mass index)	Ordered categorical
	Fitness level measured using the 20-mSRT	Ordered categorical
	Knowledge of the health benefits of physical activity	Ordered categorical
	Attitude toward Physical activity	Ordered categorical
	Self efficacy	Ordered categorical
	Perceived behavioural control and intention	Ordered categorical
	Social Norms and Social support,	Ordered categorical
	Policy or programme changes	Qualitative

At baseline, bivariate analysis (cross tabulation) will be used to compare the differences in proportions of the primary and secondary outcome measures of the experimental and control groups. Chi-square test (X^2^) will be used for significance testing of the self-reported physical activity levels (dependent ordered categorical variable) and other categorical independent variables while repeated measures ANOVA will be used for Step count (average steps/day). Based on data generated using bivariate analysis, all independent variables which are significant at 10% will be incorporated into the regression model.

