Regression analysis will be used to assess the extent to which the independent variables predict self-reported physical activity levels and step count (average steps/day). Level of significance will be 5% at 95% confidence interval. The effect of the intervention will be tested using multilevel mixed effects models for repeated measures adjusted for relevant confounding factors. This approach ensures that the longitudinal and hierarchical structure of the data are considered in the analysis. Because of the clustered structure of the data, random effects for the cities and schools will be included in all analyses.

The qualitative data will be transcribed, coded, entered into NVIVO version 10 and analyzed using thematic approach. Points of agreement and disagreement among discussants with reference to the study objectives will be noted.

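### Policy and built-environment scores from only 22 schools are to be grouped for analysis; a median split would lose about 36% of the information and other cuts about 10% to 46% or more (normal score assumed)

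*Protocol article*

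**What the plan says.** Four places in the Protocol article bear on this.

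- **S-PAPA** (Data collection, item ii). Teachers complete this school policy tool, and its totals are grouped: "Total point scores will also be either median-split into high- and low or stratified by percentile for analysis". The number of strata is not given.
- **SPEEDY** (Data collection, item iii). The checklist "can be scored to quantify environmental support for physical activity", yet "The scores from each of the key variables will be dichotomised into low and high based on percentiles". The same sentence adds that a school suitability index will be computed. Table 2 lists built environment as ordered categorical.
- **Aim.** The Abstract states: "The aim of the proposed study is to identify factors influencing; and evaluate the effects of a multi-level intervention". Table 1 gives the corresponding objective: "Identify factors (individual, social-cultural, built environment and policy) influencing physical activity of in-school adolescents".
- **Units and analysis.** Blinding and sampling technique fixes the number of schools: "Twenty two schools will be pair-matched based on their ownership". Under Data management and statistical analysis, "all independent variables which are significant at 10% will be incorporated into the regression model". Random effects for schools and cities are to be included in all analyses.

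The Data collection section does provide for continuous use of self-reported activity (in some analyses) and of fitness. It says nothing similar for S-PAPA or SPEEDY.

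**The concern.** Each school supplies one S-PAPA total and one set of SPEEDY scores. With a school random effect in the model, a school-level factor is judged against the variation between 22 schools. The 1,000 pupils do not add to that number. Cutting a numeric score into groups treats every school in a group as alike, so precision is lost where the trial has fewest units.

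The 10% bivariate screen can add to this. If the grouped school scores pass through it, a real factor weakened by the cut may be dropped before the regression is fitted. For S-PAPA, the text also leaves two ways of grouping open, and these can give different answers.

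At stake is the chance of finding a policy or built-environment factor that truly matters.

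**Working it through.** The protocol gives no precision or power figure for the school-level factor analysis, so there is none to reproduce.

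**Inputs**
- Number of schools: 22 (Blinding and sampling technique).
- Significance level: "Level of significance will be 5% at 95% confidence interval", taken as two-sided.
- Assumed, because the protocol gives neither: a normal score, a linear relation with activity, and a school-level correlation r of 0.4 to 0.7.

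**Step 1. Information kept by grouping**

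For ordered groups scored by their means, the share kept is the sum over groups of P(group) × E(score | group)². For a two-group cut at percentile p this becomes φ(z_p)² / [p(1 − p)].

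At the median: φ(0)² / 0.25 = (1/2π) / 0.25 = 2/π = 0.637. The loss is 1 − 0.637 = 0.363, and 22 × 0.637 = 14.0 schools.

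| Grouping | Kept | Lost | Equivalent schools of 22 |
|---|---|---|---|
| Low/high at median | 0.637 | 36% | 14.0 |
| Low/high at 67th percentile | 0.595 | 41% | 13.1 |
| Low/high at 75th percentile | 0.539 | 46% | 11.8 |
| Low/high at 90th percentile | 0.342 | 66% | 7.5 |
| Tertiles | 0.793 | 21% | 17.5 |
| Quartiles | 0.861 | 14% | 18.9 |
| Quintiles | 0.897 | 10% | 19.7 |

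**Step 2. Other score shapes**

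A median split loses 25% if the score is uniform and 50% if it is double exponential.

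**Step 3. Power with 22 schools**

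Simulation with 20,000 runs per r and a two-sided 5% t test on the correlation (20 degrees of freedom):

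| Assumed r | Continuous | Median split | Tertiles | Low/high at 75th percentile |
|---|---|---|---|---|
| 0.4 | 47% | 30% | 38% | 27% |
| 0.5 | 69% | 46% | 56% | 40% |
| 0.6 | 87% | 65% | 77% | 57% |
| 0.7 | 97% | 83% | 92% | 75% |

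**Step 4. The SPEEDY index**

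Suppose the six named SPEEDY variables are each split at the median and then summed. This is an assumption, as the construction is left to the cited sources. With common correlation ρ, the share of the information in their continuous total that is kept is

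(2/π)(6 + 30ρ) / [6 + 30 × (2/π) × arcsin ρ].

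- ρ = 0: 0.637 × 6/6 = 0.64, a loss of about 36%.
- ρ = 0.3: 0.637 × 15 / (6 + 5.82) = 0.81, a loss of about 19%.

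**The case against.** Several arguments on the other side have weight.

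- **The grouping follows published scoring, and its details belong in an analysis plan.** It is fair that the missing percentile and number of strata are not in themselves a fault of the article. However, the text does state that the S-PAPA grouping is for analysis, and it types built environment as categorical. That is a stated choice of method, and precedent does not restore the lost information.
- **No single loss figure applies.** A reader might take about a third as the loss for every option. The documents do not support that. The 36% belongs to a median split of a roughly normal score. Finer S-PAPA strata lose less, and an off-median low/high cut loses more. Because SPEEDY variables are combined into an index, the loss for one binary variable does not carry over to it.
- **The T2 argument is thin.** A reader might infer that recomputing a median split at T2 would hide a general improvement. That would be so if it were done, but nothing says it will be. Table 1 marks built environment at T0 and T2, whereas Table 2 shows T0 only. Policy change is to be assessed qualitatively through key informant interviews.
- **The strand is exploratory.** Policy and built environment are two of the four factor domains in Table 1, and they are also studied by interviews, focus groups, observation and desk review. It would be too much to call them half of the trial's aim. Even a continuous score has only 47% power at r = 0.4, so 22 schools is itself a major limit.
- **Continuous terms carry risks.** Several school-level covariates in a model with 22 clusters invite overfitting and leverage from single schools. This stands, and the fix has to allow for it.

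**Conclusion.** The point holds as a minor improvement to the analysis. The plan commits to grouping school-level scores although only 22 schools inform the factors in question, and no text commits to analysing those scores as continuous.

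A median split loses about 36% of the information. Over assumed correlations of 0.4 to 0.6, power falls from 47–87% to 30–65%. The other groupings the wording permits lose roughly 10% (quintiles) to 46% or more (a low/high cut at the 75th percentile or beyond). These figures rest on normality, linearity and the assumed correlations, none of which the protocol states. For the SPEEDY index the loss cannot be fixed without knowing its construction.

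The consequence is confined to the exploratory identification of policy and built-environment factors. A reader might infer that the trial's main result is weakened. It is not: neither the randomised comparison nor the sample size uses these groupings.

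**What to change.** - Make the S-PAPA total and one SPEEDY summary score, built from subscales that have not been dichotomised, the main school-level covariates. Keep each continuous and standardised.
- Enter them in the mixed model one at a time, or at most sparingly, given 22 clusters. Check linearity and look for influential schools.
- Keep the high/low groups and the published suitability index as description.
- If categories are shown at more than one wave, use cut-points fixed at T0.

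This changes analysis wording only and needs no new data. The small downside is the linearity assumption, sensitivity to single schools, and less direct comparability with the cited scoring. Reporting the published index alongside reduces the last of these.

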**Methods:**

The study will adopt a cluster randomised controlled trial design and schools will serve as the unit of randomisation. The sample size is 1000 in-school adolescents aged 10–19 years. The study will be guided by the socio-ecological model and theory of reasoned action and baseline data will be obtained through a mixed methods approach comprising a cross sectional survey to document the self-reported physical activity levels coupled with objectively measured physical activity levels using pedometers for a subset of the sample. Other measurements including weight, height, waist and hip circumferences, fitness level using the 20-m shuttle run test (20-mSRT) and blood pressure will be obtained. The schools’ built environment and policy support for physical activity will be assessed using structured questionnaires coupled with key informant interviews and focus group discussions with the school authorities. Baseline findings will guide the design and implementation of a 12-week multi-level intervention. The primary outcome measures are self–reported and 7-day objectively measured physical activity. Other secondary outcome measures are body-mass-index for age, waist-to-hip ratio, cardioresiratory fitness and blood pressure. The association between behavioural factors and physical activity levels will be assessed. Follow-up measurements will be taken immediately after the intervention and 3-months post intervention.

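### The 10% trigger for a third anthropometric reading is too loose to catch height errors, so a misreading could be averaged into BMI-for-age; waist-to-hip ratio is exposed in the same way

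*Protocol article*

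**What the plan says.** Item (v) of the protocol article's Data collection section gives the rule: "Anthropometric measurements will be taken twice and averaged; for discrepancy >10%, a third measurement will be taken". It is one relative limit for all anthropometric measures. No absolute limit is given for any of them, and the text does not say how a third reading is combined with the first two.

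The same item fixes the recording units. For height, "The sliding bar will be lowered and pressed flat on the head and recorded to the nearest centimeter". For weight, "weight will be recorded to the nearest gram". For the circumferences, "Waist circumference will be measured to the nearest 0.1 cm horizontally" and "Hip circumference will be measured to the nearest 0.1 cm". The ratio is then derived: "Waist hip ratio will be obtained as waist circumference/hip circumference". BMI-for-age is classed by WHO Z-scores, with +1 SD given as 25 kg/m² and +2 SD as 30 kg/m² at 19 years. Blood pressure has its own rule, the mean of three readings, and is not affected.

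The abstract names the outcomes concerned: "Other secondary outcome measures are body-mass-index for age, waist-to-hip ratio, cardioresiratory fitness and blood pressure". Table 1 schedules the underlying measurements at T0, T1 and T2, and Table 4 lists the BMI outcome as ordered categorical.

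**The concern.** Duplicate readings are taken to catch slips in reading or recording. A percentage limit suits a quantity that varies from zero, but a student's height is a large number measured with small error, so 10% of it is a very wide band. A 10 cm digit slip is within 10% for anyone taller than 100 cm, which in practice means every participant aged 10 to 19. The rule would therefore pass the kind of error it is there to find, and the average would then look plausible.

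Height enters BMI squared, so a relative error in mean height is roughly doubled. Because the same students are followed over three visits, an error accepted at one visit appears as change within that student, and where BMI is analysed in classes it can move a student near a cut-off into the wrong class.

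**Working it through.** The 10% limit is stated without derivation, so there is no figure of the plan to reproduce. The check asks what the limit lets through.

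**Inputs.** From the protocol: the 10% limit, averaging of two readings, the 1 cm height unit, and the cut-offs of 25 and 30 kg/m² at 19 years. Assumed, because the protocol gives no body sizes: heights of 130 to 180 cm, a waist-to-hip ratio of 0.80, and the reading SDs in step 5.

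**1. Tolerance for height.** 0.10 × height gives 13 cm at 130 cm, 15 cm at 150 cm, 16 cm at 160 cm and 18 cm at 180 cm. The base of the percentage is not stated. For a true 160 cm with the second reading too high, the permitted gap is 16.0 cm on the correct reading, 160 × 1.05/0.95 − 160 = 16.8 cm on the mean of the pair, and 160/0.9 − 160 = 17.8 cm on the larger reading. All are at least 16 recording units.

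**2. Effect on BMI of one wrong height.** If one reading is off by a fraction e, the mean is off by e/2 and BMI is multiplied by 1/(1 + e/2)².
- Readings of 160 and 170 cm: mean 165 cm, factor (160/165)² = 0.940, so −6.0%.
- e = +10%: 1/1.05² = 0.907, so −9.3%.
- e = −10%: 1/0.95² = 1.108, so +10.8%.

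The ±10% cases take the percentage on the correct reading; another base shifts these bounds slightly.

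**3. Effect on BMI class at 19 years.** With the 160/170 cm slip, a true BMI of 26.0 reads 26.0 × 0.940 = 24.4, below the overweight cut-off. At the limit, with one height 10% too low, a true 25 × 0.95² = 22.6 reads as 25, and a true 30 × 0.95² = 27.1 reads as 30.

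**4. Weight and waist.** One weight reading off by 10% shifts mean weight, and hence BMI, by 5%. One waist reading off by 10% multiplies the ratio by 0.95 or 1.05: 0.80 becomes 0.76 or 0.84. If waist and hip each have one reading off by 10% in opposite directions, the range is 0.80 × 0.95/1.05 = 0.72 to 0.80 × 1.05/0.95 = 0.88.

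**5. How often the rule would act for height.** With independent normal reading errors of SD s, the difference of two readings has SD √2 × s. For s = 3 cm, 16/(1.414 × 3) = 3.77, a two-sided probability of about 0.02%. For s = 2 cm or less it is effectively zero. Even at an implausible s = 5 cm it is about 2.4%.

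**The case against.** The strongest reply concerns consequence. The figures at the limit are worst cases, and no expected error is known. If duplicate heights usually agree closely, the rule seldom acts because there is little to catch. Ordinary reading error costs little: with an assumed reading SD of 1 to 3 cm at 160 cm and BMI 19.5, the mean of two readings adds a BMI error with SD 2 × 19.5 × (s/√2)/160, about 0.17 to 0.52. Against an assumed between-student SD of 4 to 2, that raises cross-sectional variance by (0.17/4)² ≈ 0.2% to (0.52/2)² ≈ 7%. This stands, although the share would be larger for within-student change.

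It also stands that the rule is the same in both arms, so no directional bias is shown. The primary outcomes, self-reported activity and step count, are untouched. Waist-to-hip ratio is an outcome in the abstract but is not listed in Tables 2 or 4.

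The protocol has other safeguards: standard procedures for height and weight, trained assistants, scale calibration and daily checks of the height scale (Reliability), and data cleaning (Data management and statistical analysis). These help only in part. Calibration addresses the instrument, not a misreading. Cleaning is described generally and might flag two discrepant heights if both are kept, but it cannot supply the repeat reading afterwards.

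Two stronger readings are tempting. A reader might infer that the accepted errors swamp any effect a 12-week programme could have. The protocol gives no expected effect on BMI or waist-to-hip ratio, and that comparison sets one student's worst-case error against a mean over about 500 students per arm. A reader might also infer that a tolerance wider than the recording unit is a contradiction. It is not: resolution and repeat tolerance are different things.

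**Conclusion.** The point holds as a weakness in a rule that the protocol itself states, not as a missing detail. No other section sets a tighter limit. For height the check is close to inert, and this does not depend on the height assumed within 130 to 180 cm. A 10 cm slip costs about 6% of BMI in the student concerned, and the bounds at the limit are -9.3% and +10.8%. The waist-to-hip shift of 0.04 either way rests on an assumed ratio of 0.80.

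These are errors that the rule allows, with unknown frequency. The expected result is some loss of precision and some misclassification near BMI-for-age cut-offs, in secondary outcomes only and without a known direction. The documents do not support a claim that gross errors will occur or that the trial's main conclusions are at risk.

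**What to change.** Before baseline, replace the single 10% rule with an absolute limit for each measure, taken from the standard anthropometric procedure that the trial adopts. For illustration only: about 0.5 to 1 cm for height, 0.2 kg for weight, and 1 cm for waist and hip. Record height finely enough to apply its limit; the present unit, "pressed flat on the head and recorded to the nearest centimeter", is too coarse for a limit of 0.5 cm. State how the third reading is used, for example the median of the three. Apply the rule in both arms at T0, T1 and T2.

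The cost is a short change to the measurement procedure, more third readings, and slightly longer sessions for about 1,000 students at three visits, with the same staff and equipment. The change has to come before data collection, because a repeat reading that was not taken cannot be recovered in the analysis.
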